### 1.3 Study Rationale

Given interest in preoperative S-PBI, there have been several recently initiated preoperative S-PBI trials that have opened and are ongoing (see Table 1). However, these ongoing preoperative trials are predominantly using doses seen in the adjuvant setting as established with IORT, primarily 21Gy/1Fx, although a 3-fraction and 5-fraction regimen are also currently being investigated at Moffit (NCT03137693) and the Juravinski Cancer Center (NCT02065960), respectively. Pathologic complete response rates with three-fraction preoperative S-PBI have been reported to be 36%, with the highest pCR rate of 67% in the 25.5Gy/3Fx cohort, though this cohort was small with only 6 patients (Bondiau IJROBP 2013), suggesting room for improvement. At ESTRO in 4-2019, the results from the Netherlands (clinical trials.gov: NCT0231661) ABLATIVE trial treating patients with Estrogen positive her2- tumors and 20 Gy preoperative radiation yielded a path CR of 33% at 6 months and 41% at 8 months with mild treatment toxicity (ESTRO abstract OC-0591 Vasmel et al.)

As predicted by the universal survival curve, 38Gy/1Fx would be equivalent to 70Gy/35Fx, a dose that is typically used for gross disease (Park IJROBP 2008). Given that these early studies have reported minimal toxicity with the addition of preoperative S-PBI, this offers promise that further dose escalation to achieve a radioablative dose adequate for gross disease may be feasible.

Therefore, the purpose of this phase I trial is to evaluate dose-limiting toxicity while dose escalating single-fraction preoperative S-PBI to a presumed radioablative dose over 3 cohorts, starting with 30Gy in 1 fraction and advancing to 34Gy and 38Gy in 1 fraction. This would be accomplished on the MR Linac, CyberKnife, or GammaPod. The GammaPod is a novel device dedicated to S-PBI utilizing a Cobalt-60 source (Yu Med Phys 2013), which offers a highly reproducible prone setup with a mean of 1.8mm of mismatch reported in 15 patients at the University of Maryland on consecutive scans (Yu JCO 2011). Implications of this research are far reaching, including determination of the maximally tolerated dose for preoperative S-PBI, pathologic complete response rates of early stage breast cancer to a predicted radioablative dose, radiographic markers of treatment response (radiomics), and translational research assessing mechanisms of immune and radiation response.

## 2.0 STUDY OBJECTIVES

### 2.1 Primary Objectives

- 2.1.1 The primary objective is to escalate the dose of 1 fraction stereotactic partial breast radiotherapy utilizing the MR Linac, Gammapod or Cyberknife system to an ablative dose in the pre-operative setting to the primary tumor without exceeding the maximum tolerated dose in patients with early stage breast cancer.

### 2.2 Secondary Objectives

- 2.2.1 Local Control
- 2.2.2 Acute Toxicity (90 Days)
- 2.2.3 Late Toxicity (24 months)
- 2.2.4 Rates of Surgical Morbidity
- 2.2.5 Pathologic Complete Response Rates
- 2.2.6 Patient and Physician Cosmesis Outcomes
- 2.2.7 Distant Disease-Free Survival

### 2.3 Exploratory Objectives

#### 2.3.1 Radiomics on MRI

Through extracting and analyzing a large number of features from medical imaging, radiomics has shown promising results in treatment outcome prediction for many diseases including breast cancer (45-50). UTSW physics group has developed several new radiomic approaches and radiomic features, such as a multi-objective radiomics model (51) and a new radiomic "Shell" feature (52). As an exploratory end point for this trial, we will explore the application radiomics using pre-treatment MRI, treatment parameters and clinical characteristics as input to predict pathological response of radiation therapy (XRT) based on pathology report of surgical tissues and local recurrence.

#### 2.3.2 Optional Translational correlates using blood samples and tissue samples from core biopsies and surgical tissue post-radiation

- Primary tumor biopsies (pending volume of tissue)
  - Expression of PD-L1, PD-L2, PD1, CD3, CD68, CD8, Ki67.
  - RNAseq analyses including RNA profiling.
  - Whole exome sequencing to determine mutational burden and neoantigen detection.
  - T-cell receptor sequencing to determine intratumoral TCR diversity.
  - IHC to quantify immune populations.
- Blood (both Serum and PBMC)
  - T-cell receptor sequencing to determine tumor-specific TCR diversity, expansion and contraction.
  - Analysis of antibody response (both quantitative antibody titer and qualitative antibody binding and functionality).
  - Study of T-cell composition and functioning.
  - Identification of circulating antigen, DNA or tumor cells.

- Analysis of cytokine response.
- Analysis of blood cell composition using flow cytometry or mass cytometry.
- Analysis of inflammatory status

## 2.4 Endpoints

The primary endpoint of the phase I portion is to either reach the maximum tolerated dose (MTD) or a dose of 38 Gy (whichever comes first) by escalating the dose of S-PBI toward the tumorcidal dose of 38 Gy in 1 fraction. Patients will be treated in cohorts of seven to fifteen. Toxicity will be graded using the NCI Common Toxicity Criteria for Adverse Events (CTCAE) v. 5.0. ***A dose-limiting toxicity (DLT) is a grade 3 toxicity deemed definitely related to treatment in the following categories: skin, rib bone (fracture), pulmonary (radiation pneumonitis), or neurological (injury to intercostal or brachial plexus nerves) or any grade 4 or 5 toxicity deemed definitely attributed to the therapy.*** All reported DLTs will be verified by study chair, data and safety monitoring committee, and, as appropriate, independent review before final determination that a DLT has in fact occurred. Doses will be escalated an additional 3.5-4 Gy per treatment. The phase I portion of the study will be completed when either of the following events occur: 1) the MTD for a cohort is reached or 2) when the highest protocol dose of 38 Gy, which the investigators have determined to be likely efficacious in controlling gross disease, is achieved and tolerated.

## 3.0 SUBJECT ELIGIBILITY

Eligibility waivers are not recommended; however, if warranted, prior approvals are required per Section 11.6.1. Subjects must meet all of the inclusion and exclusion criteria to be registered to the study. Study treatment may not begin until a subject is registered. Once registered, a subject is still required to meet all inclusion and exclusion criteria on the first day of treatment, prior to treatment.

### 3.1 Inclusion Criteria

1. Invasive epithelial (ductal, medullary, lobular, papillary, mucinous (colloid), or tubular) histologies of the breast 3 cm or less (T1-T2cN0) in women who have not undergone surgery or neoadjuvant endocrine or chemotherapy for current breast cancer diagnosis
2. Tumor must not involve the overlying skin based on imaging evaluation and/or clinical exam
3. Age  $\geq$  18 years old and female
4. Greatest Tumor dimension is 3cm or less based on US. MRI measurements can be included only if performed BEFORE the biopsy
5. Tumor must be unifocal
6. The tumor must be visible on CT scan and/or preferably marked with clip(s) in tumor
7. Patients must undergo an MRI for work up to aid in tumor delineation and to rule out additional foci of disease. If additional foci of disease are present, they need to have a negative biopsy to proceed with treatment. If patient cannot have MRI, contrast enhanced digital mammography (CEDM) is allowed in place of MRI.
8. Clinically and radiographically node negative on ultrasound of the axilla or MRI
9. Estrogen receptor positive or Progesterone receptor positive and Her2neu negative
10. Ability to understand and the willingness to sign a written informed consent.
11. Women of child-bearing potential must agree to use adequate contraception (hormonal or barrier method of birth control) prior to the start of study and for the duration of radiation therapy. Should a woman become

pregnant or suspect she is pregnant while participating in this study, she should inform her treating physician immediately

A female of child-bearing potential is any woman (regardless of sexual orientation, having undergone a tubal ligation, or remaining celibate by choice) who meets the following criteria:

- Has not undergone a hysterectomy or bilateral oophorectomy; or
- Has not been naturally postmenopausal for at least 12 consecutive months (i.e., has had menses at any time in the preceding 12 consecutive months)

### 3.2 Exclusion Criteria

1. Multi-centric disease
2. Prior RT to the involved breast
3. Tumor size >3cm
4. Uncontrolled intercurrent illness including, but not limited to, ongoing or active infection, symptomatic congestive heart failure, unstable angina pectoris, cardiac arrhythmia, or psychiatric illness/social situations that, in the opinion of the investigator, would limit compliance with study requirements
5. Patients who are pregnant or lactating due to the potential exposure to the fetus to radiation therapy and unknown effects of radiation therapy to lactating females
6. Patients unable to have an MRI or contrast enhanced digital mammography (CEDM)
7. Prior ipsilateral breast cancer
8. Tumor less than 5mm from the skin surface on clinical exam and/or radiographic imaging
9. Patients with active Lupus or scleroderma

## 4.0 TREATMENT PLAN

### 4.1 Treatment Dosage and Administration

The term “stereotactic” for the purposes of this protocol implies the targeting, planning, and directing of therapy using beams of radiation along any trajectory in 3-D space guided by one or several fiducials of known 3-D coordinates. This differs from conventional radiation therapy in which therapy is directed toward skin marks or bony landmarks and assumed to correlate to the actual tumor target based on a historical simulation. It should be understood that SBRT has become a treatment that is well beyond just stereotactic targeting. Indeed SBRT is mostly about high dose per fraction, accounting properly for errors including motion, careful construction of dosimetry that compacts high dose into the tumor and not normal tissues, and extra careful treatment conduct. This protocol will require treatments to be conducted with the use of the MR Linac, Cyberknife system® utilizing its techniques of continuous image guidance and targeting corrections for quality assurance during treatment, or the Gammapod which utilizes a vacuum assisted breast cup for immobilization.

#### Technical Factors

The Cyberknife system® with its 6 MV linear accelerator will be required for radiation delivery by the protocol, MR Linac, or the Gammapod which delivers radiation with cobalt sources. Other treatment delivery options will not be considered.

**4.1.1 All patients in each dose cohort will be treated as a single group for dose escalation. The starting dose for the dose escalation portion will be 30 Gy. Subsequent cohorts of patients will receive an additional 3.5-4 Gy per treatment. If significant toxicity is encountered at the starting dose, a de-**

escalation will occur (step -1) to 26.5 Gy. If at the time of this trial opening, we have completed our ongoing adjuvant single fraction stereotactic partial breast irradiation trial dose cohort 30 Gy, and have deemed its safe, we will skip the 30 Gy arm and start at 34 Gy for this trial. Based on modeling from the universal survival curve, 38 Gy in 1 fraction is roughly biologically equivalent to the dose of 70 Gy which is the dose commonly used to treat gross disease.

| Level | Dose    | No. of Patients |
|-------|---------|-----------------|
| -1    | 26.5 Gy | 7-15            |
| 1     | 30 Gy   | 7-15            |
| 2     | 34 Gy   | 7-15            |
| 3     | 38 Gy   | 7-15            |

Prescription will be minimum of 27 Gy to the PTV for all dose cohorts, and either 30 Gy, 34 Gy, or 38 Gy to the GTV/CTV per appropriate dose cohort.

Minimum waiting periods will be assigned between each dose cohort to evaluate toxicity. The phase I study will be completed when dose limiting toxicity is reached or when the highest protocol dose of 38 Gy, which the investigators have determined to be likely efficacious in controlling gross disease, is achieved and tolerated.

At the time of writing this protocol, the current single fraction trial being tested in the adjuvant setting for early stage breast cancer is 30 Gy in 1 fraction at UTSW (clinical trials.gov number NCT02685332). If we meet our accrual goal and waiting period without a dose limiting toxicity by the time this protocol is ready to go live, we will start our dose for this trial at 34 Gy rather than 30 Gy.

Treatment can be done on MR Linac, the Gammapod or Cyberknife.

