## STUDY SCHEMA

### Phase I Study of Pre-Operative Stereotactic Partial Breast Irradiation Therapy for Early Stage Breast Cancer

[figure not shown]

\*\*Of note, after pre-operative radiation and prior to surgery, patients should start endocrine therapy within 21 days after pre-operative radiation but it is encouraged to start the day after post-radiation biopsy.

Prescription will be 30 Gy to the Planning Target Volume (PTV) for all dose cohorts, and either 30 Gy, 34 Gy, or 38 Gy to the GTV/CTV per appropriate dose cohort.

Number of patients= between 7-60 for phase I (depending on tolerance)

All patients in each dose cohort will be treated as a single group for dose escalation. The starting dose for the dose escalation portion will be 30 Gy. Subsequent cohorts of patients will receive an additional 4 Gy per treatment. If significant toxicity is encountered at the starting dose, a de-escalation will occur (step -1) to 26.5 Gy. As we are currently concluding an adjuvant single fraction phase I protocol (ClinicalTrials.gov Identifier: NCT02685332) to 30 Gy in a single fraction for early stage breast cancer, if we meet our endpoints of this study, we will start our dose escalation at 34 Gy instead of the 30 Gy, as safety of the 30 Gy arm will have already been established.

| Level | Dose    | No. of Patients |
|-------|---------|-----------------|
| -1    | 26.5 Gy | 7-15            |
| 1     | 30 Gy   | 7-15            |
| 2     | 34 Gy   | 7-15            |
| 3     | 38 Gy   | 7-15            |

- Prescription will be a minimum of 27 Gy to the PTV for all dose cohorts, and either 30 Gy, 34 Gy, or 38 Gy to the GTV/CTV per appropriate dose cohort. See section 4.1.5

Minimum waiting periods will be assigned between each dose cohort to evaluate toxicity. The phase I study will be completed when dose limiting toxicity is reached or when delivery of a pre-determined highest dose of radiation (38 Gy) that has been deemed likely to be efficacious for treatment of early stage breast cancer is attained.

At the time of writing this protocol, the current single fraction trial being tested in the adjuvant setting for early stage breast cancer is 30 Gy in 1 fraction at UTSW (NCT02685332). If we meet our accrual goal and waiting period without a dose limiting toxicity by the time this protocol is ready to go live, we will start our dose for this trial at 34 Gy.

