| Number of Subjects                     | Between 7-60 patients (depending on tolerance)                                                                                                                                                                                                                                                                                                                                                          |
| Diagnosis and Main Inclusion Criteria  | Invasive epithelial (ductal, medullary, lobular, papillary, mucinous (colloid), or tubular histologies of the breast 3 cm or less T1-T2cN0 whom have not undergone surgery or neoadjuvant systemic therapy.                                                                                                                                                                                             |
| Study Product(s), Dose, Route, Regimen | Radiation, Stereotactic Body Radiation Therapy
1 fraction SPBI, dose escalation 3.5-4 Gy per cohort
30Gy→38Gy (3 dose cohorts, potentially 2 if 30 Gy dose is proven safe on current ongoing trial before the start of this trial)                                                                                                                                                                |
| Duration of administration             | One day                                                                                                                                                                                                                                                                                                                                                                                                 |
| Reference therapy                      | Postoperative Single fraction Radiation Therapy                                                                                                                                                                                                                                                                                                                                                         |

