#### **4.1.5 Radiation Planning and Target Goals for MR LINAC, Gammapod and Cyberknife:**

- 95% of the PTV should receive a minimum of 27 Gy and 99% of the target volume (GTV) receives a minimum of 93% of the prescription dose. Minor deviation if 90% of PTV receives 27 Gy. All efforts should be made to meet the skin constraint even if PTV coverage will be compromised. In this situation, would prioritize skin, brachial plexus, and spinal cord constraint over PTV coverage and this is acceptable and not a deviation, and will not be deemed a protocol violation if PTV coverage not met in order to meet these OAR constraints. Efforts should be made to keep the PTV volume coverage to a minimum dose of 27 Gy to 95% of volume. In the situation when the GTV is close to skin, prioritize the skin constraint over GTV coverage.
- Max hot spot < 130% of the prescription dose is recommended
- Prescription will be either 30 Gy, 34 Gy, or 38 Gy to the GTV/CTV per appropriate dose cohort.

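### Level -1 (26.5 Gy) has no usable prescription: the 27 Gy PTV minimum set for all cohorts exceeds it, and 26.5 Gy is never listed as a tumor dose

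*Protocol*

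**What the plan says.** The dose tables in the Study Schema and Section 4.1.1 have four rows: level -1 at 26.5 Gy, then 30, 34 and 38 Gy, each with 7-15 patients. The route to level -1 is: "If significant toxicity is encountered at the starting dose, a de-escalation will occur (step -1) to 26.5 Gy".

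For planning, Section 4.1.1 states: "Prescription will be minimum of 27 Gy to the PTV for all dose cohorts, and either 30 Gy, 34 Gy, or 38 Gy"; the last three are GTV/CTV doses. The schema carries the same rule below its table ("Prescription will be a minimum of 27 Gy to the PTV for all dose cohorts"), but above the table it says: "Prescription will be 30 Gy to the Planning Target Volume (PTV) for all dose cohorts". Section 4.1.5 sets the goal as "95% of the PTV should receive a minimum of 27 Gy", and Section 4.1.6 repeats it. In both, the minor deviation relaxes the volume to 90% of the PTV and leaves the dose at 27 Gy. Section 4.1.5 again lists only 30, 34 or 38 Gy for the GTV/CTV.

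The Study Summary describes "3 dose cohorts, potentially 2 if 30 Gy dose is proven safe on current ongoing trial". If the adjuvant trial has cleared 30 Gy, Section 4.1.1 says "we will skip the 30 Gy arm and start at 34 Gy for this trial".

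Section 7.4 sends the reader to Section 10.1 for stopping. That section ends the study at a 90-day DLT rate of 33% or more and defines the MTD as the next lower level that was tolerated. It contains no de-escalation step.

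**The concern.** Level -1 is the protocol's response to excess toxicity in the first cohort. A planner opening it would find a margin-dose floor above the cohort's nominal tumor dose, no tumor prescription at 26.5 Gy, and a schema with two different PTV doses. Followed as written, the required dose at the PTV margin would be what it was at the level just judged too toxic. The cohort's 90-day DLT data would then be labeled 26.5 Gy while coming from plans that are not clearly 26.5 Gy plans, and the MTD could be reported from them.

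**Working it through.** **Inputs.** Level doses 26.5, 30, 34 and 38 Gy, with up to 15 patients per level (schema, 4.1.1). PTV minimum 27 Gy (schema, 4.1.1, 4.1.5, 4.1.6). 99% of the GTV at 93% of prescription or more, and a recommended hot spot below 130% (4.1.5). CTV equal to GTV, and PTV equal to CTV plus 3-10 mm (4.1.4). Cap of 60 patients (10.2).

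**Is level -1 a planned cohort?** 4 levels x 15 = 60, which matches the cap; three levels would give 3 x 15 = 45. This supports the table's plain meaning but does not prove it, because no path through the stated rules fills all four levels.

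**PTV minimum relative to prescription**

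| Level dose (Gy) | 27 / dose | Schema's 30 / dose |
|---|---|---|
| 26.5 | 101.9% | 113.2% |
| 30 | 90.0% | 100.0% |
| 34 | 79.4% | 88.2% |
| 38 | 71.1% | 78.9% |

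The 27 Gy floor exceeds the tumor dose only at level -1.

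**What de-escalation from 30 Gy changes.** Tumor prescription: 30 - 26.5 = 3.5 Gy, and 3.5/30 = 11.7%. PTV minimum: 27 - 27 = 0. GTV floor: 0.93 x 30 = 27.9 Gy against 0.93 x 26.5 = 24.6 Gy, an intended gap of 3.3 Gy. If the enclosed GTV receives at least the PTV minimum, the gap is 27.9 - 27 = 0.9 Gy.

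**How much of the tumor is held at 27 Gy or more.** Assume a spherical tumor of radius r and a margin m not trimmed at skin or chest wall. The GTV share of the PTV is f = (r/(r+m))^3. At most 5% of the PTV may fall below 27 Gy, so the GTV share at 27 Gy or more is at least 1 - 0.05/f. For a 2 cm tumor:

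- 3 mm margin: f = 0.455, share at least 89%
- 5 mm margin: f = 0.296, share at least 83%
- 10 mm margin: f = 0.125, share at least 60%

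For a 1 cm tumor with a 10 mm margin, f = 0.037 and the bound is 0. That would need a cold center, while Section 4.1.6 requires the maximum to lie in the CTV for Cyberknife and MR Linac.

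**Is such a plan deliverable?** 1.30 x 26.5 = 34.45 Gy, which is above 27 Gy, so yes.

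**How often the branch is reached.** A starting level fails with 3 or more DLTs in the first 9. The DLT rate is an assumption. P(X >= 3 | n = 9) is 0.8% at a rate of 5%, 5.3% at 10%, 26% at 20% and 62% at one third.

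**Example of a coherent floor.** 0.90 x 26.5 = 23.85 Gy, about 23.9 Gy, using the 27/30 ratio of the 30 Gy cohort.

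**The case against.** **The 27 Gy sentence may not reach level -1.** It goes on to name 30, 34 and 38 Gy, and the Study Summary counts three cohorts. On that reading the floor is coherent wherever it applies. This is a fair reading, but it leaves level -1 with no PTV or GTV/CTV rule at all, so the gap changes form and does not close.

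**PTV coverage may be compromised.** Sections 4.1.5 and 4.1.6 excuse a shortfall made to meet skin, brachial plexus or spinal cord limits, and the organ limits in the dose-volume table do not vary by dose level. This stands as a qualification: where those limits bind, the margin dose can fall, and several DLT categories are partly protected by fixed limits. It does not supply a level -1 prescription.

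**The branch is unlikely.** The background reports one DLT among 75 analyzable patients in the five-fraction adjuvant trial and none among 32 in a preoperative single-fraction trial up to 21 Gy. The doses and schedules differ, but nothing there points to a rate of 20% or more. No escalation decision at 30, 34 or 38 Gy is affected.

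**Two stronger readings go too far.** A reader might infer that a 26.5 Gy cohort cannot be treated; the hot-spot allowance shows that it can. A reader might also infer that Sections 4.1.1 and 10.1 prescribe rival fallback doses after a failed 34 Gy start, 26.5 Gy against 30 Gy. The text does not support that. The starting dose named in the de-escalation sentence has just been fixed at 30 Gy, and step -1 is the level directly below 30 Gy. Moreover, 4.1.1 names a cohort to open, whereas 10.1 defines the MTD to report and opens none.

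**Conclusion.** The point holds for the level -1 dose line and for the schema. Taken literally, level -1 carries a margin floor at 101.9% of its own tumor dose; taken narrowly, it has no planning rule. Neither reading gives a 26.5 Gy GTV/CTV prescription. The schema's two PTV doses contradict each other whichever reading is taken, although its cross-reference to Section 4.1.5 shows that 27 Gy governs.

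On stopping, only a clarification is needed. Section 10.1 omits the step that 4.1.1 describes. After a failed 34 Gy start, its MTD rule would point to 30 Gy. The schema treats that dose as cleared by the adjuvant trial ("as safety of the 30 Gy arm will have already been established"), but no patient in this trial would have received it.

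The ratios and the zero change in margin dose follow directly from stated doses. The tumor-share figures rest on spherical, untrimmed volumes, and the failure probabilities on assumed DLT rates. The consequence is confined to a failed starting level. It is still worth correcting, because it concerns the dosing of a safety step and the correction is cheap.

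**What to change.** 1. In the schema and Sections 4.1.1, 4.1.5 and 4.1.6, add 26.5 Gy as the GTV/CTV prescription for level -1, with its own PTV minimum below 26.5 Gy. About 23.9 Gy would keep the 90% ratio of the 30 Gy cohort; the figure is the investigators' choice. Apply it to the minor-deviation wording too.
2. Delete the schema sentence that gives 30 Gy to the PTV for every cohort.
3. As a clarification, put the step to 26.5 Gy into Section 10.1, triggered by the existing DLT boundaries. State separately what follows a failed 34 Gy start: whether a 30 Gy cohort opens, or 30 Gy is reported as the MTD on the adjuvant evidence alone.

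Items 1 and 2 are amendment wording only. Under item 3, opening 30 Gy after 34 Gy could add 7-15 patients and their 90-day follow-up. Even if 34, 30 and 26.5 Gy all filled, that is 3 x 15 = 45 patients, within the cap of 60.
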